### Study population

Patients who have undergone CT that has detected a pulmonary nodule and was performed for a reason other than suspicion of lung cancer will be reviewed for study eligibility (box 1).

Box 1Patient eligibility criteriaInclusion criteriaPatients aged 35 years or over.Patients with a baseline CT study with at least one incidentally detected solid or part-solid pulmonary nodule that is 5–30 mm in maximum axial diameter for the whole lesion, measured using manual electronic callipers, and that is not fully calcified. The solid component of the part-solid nodule must be ≥80% of the total nodule size.Patients with a baseline CT study which includes at least one series with acquisition parameters which meet Virtual Nodule Clinic requirements.The patient has a baseline CT study that includes at least one series that comprises at least one full-inspiration breath-hold scan without a high degree of contrast media and does not exhibit quality issues (eg, motion artefacts).Exclusion criteriaPatients who received a diagnosis of cancer in the last 5 years.Patients who have thoracic implants that adversely impact the imaging appearances of the nodule.Patients who have more than five reported pulmonary nodules of any size or type, excluding fully calcified nodules (a marker of prior granulomatous infection) or metastatic lung cancer.Patients who have one or more additional nodules that are already undergoing follow-up according to pulmonary nodule management standard care.Patients who have one or more additional nodules that are pure ground glass opacity of 5 mm in maximum axial diameter for the whole lesion measured using manual electronic callipers.Patients who have one or more additional nodules >30 mm in maximum axial diameter for the whole lesion measured using manual electronic callipers.Patients with part-solid nodules where the solid component is <80% of the total nodule size.

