### AI model

The output of the LCP is a risk score that is an integer from 1 to 10 and forms part of Optellum’s VNC patient management software. A score of 1 indicates the nodule is highly likely to be benign, while a score of 10 is most likely to be malignant. The AI model underpinning the LCP is the LCP-CNN, the raw score available to researchers as a continuous value from 0 to 100, as previously reported. LCP-CNN was derived and internally validated using data from diverse populations from the USA and UK. The model was then externally validated in two independent cohorts of patients with incidentally detected pulmonary nodules, amounting to over 1500 patients in aggregate.^7 8^

In this study, the LCP will be compared with standard care in three ways:

LCP as an integer (1–10) risk score to aid physician decision-making (physician guided by AI score).LCP-CNN alone as a threshold-based rule-out recommendation (AI binary decision to discharge or not).LCP-CNN combined with a threshold-based rule-out recommendation to aid physician decision-making (physician guided by AI with binary recommendation to discharge or not).

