### Data collection

Study teams at the 12 NHS Trusts from which patients will be recruited will identify eligible patients and obtain informed consent. Consent will be obtained verbally (for patients who would not normally come on-site as part of standard care) or via written consent. Consent will be sought to analyse standard-care CT scans, associated clinical meta-data collection and the health economics assessment.

Once a patient has given consent and enrolled into the study, their baseline CT scan will be sent to VNC. Authorised research staff will then log into VNC, select the nodules of interest and record the LCP score for that nodule. The local standard nodule service decision-makers will provide a standard-care decision for eligible, consented patients via their usual nodule management pathway. The standard-care decision for eligible consented patients will then be recorded in an electronic case report form (eCRF) without knowing the LCP score.

To assess LCP under scenario #1 as described under AI model, the clinical team will thereafter be given the LCP score and relevant patient data in the nodule MDT or as part of a separate research meeting. At this point, the clinical team should remain blinded to the outcome of any actual-care investigation (eg, positron emission tomography (PET)/CT scan, biopsy). Their decision on the next management step, had they been guided by the LCP score, will then be recorded in the eCRF. The clinical team will have the option to modify management at this point. Any modification of management will be recorded in the eCRF.

Subsequent follow-up images for each patient will be sent to the VNC over the course of their nodule follow-up, and the final nodule diagnosis will be recorded. Since standard patient care can sometimes deviate from BTS guidelines, all participating sites will also collect information on patient and nodule characteristics necessary to follow the BTS guidelines. In this way, AI-guided management can be compared with BTS-compliant management. Other data points necessary to evaluate service utilisation (eg, additional scans, biopsies and treatments for lung nodules or lung cancers) will also be recorded in the eCRF.

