### Outcome measures

The outcome measures for the primary and secondary objectives are outlined in table 1.

**Table 1 T1:** Study objectives and outcome measures

Objective	Outcome measure
Primary: Determine the potential effect of the LCP on discharge	The measured difference between standard care and the three LCP-based options described under AI model for: No and percentage of cancer patients discharged (straight after assessment of the baseline scan). No and percentage of benign-nodule patients discharged (straight after assessment of the baseline scan).
Secondary: Determine the potential effect of the LCP on possible adherence to clinical guidelines	The measured difference between standard care and the three LCP-based options described under AI model: No and percentage of patients for whom a validated risk model (Brock or LCP) is used to guide the next clinical management step (ie, counting the instances where Brock is not used or where LCP is not possible to compute, or it is ignored).
Secondary: Determine the potential effect of the LCP on overall clinical management, as well as scan and procedure utilisation	No and percentage of cancer patients for whom there would have been a change in clinical management according to each of the three LCP-based options described under AI model compared with actual care (correctly for more aggressive management and incorrectly for less aggressive management). No and percentage of benign-nodule patients for whom there would have been a change in clinical management according to each of the three LCP-based options described under AI model compared with actual care (incorrectly by more aggressive management and correctly for less aggressive management). The measured difference between standard care and the three LCP-based options described under AI model for: No and percentage of CT scans and PET/CT scans performed on benign-nodule patients. No and percentage of non-surgical biopsies performed on benign-nodule patients. No and percentage of surgical excisions on benign-nodule patients.

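### The adherence outcome compares Brock use in routine care with LCP use in patients pre-selected for LCP-compatible scans, and for option 2 LCP use is about 100% by construction

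*Protocol article*

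**What the plan says.** In the protocol article, Table 1 (Outcome measures) defines the secondary outcome on adherence to clinical guidelines as "No and percentage of patients for whom a validated risk model (Brock or LCP) is used to guide the next clinical management step". It is to be compared between standard care and each of the three LCP options. The same cell names the failures: "counting the instances where Brock is not used or where LCP is not possible to compute, or it is ignored".

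Two inclusion criteria in Box 1 (Study population) bear on whether LCP can be computed. One is "Patients with a baseline CT study which includes at least one series with acquisition parameters which meet Virtual Nodule Clinic requirements". The other asks for a series with a "full-inspiration breath-hold scan without a high degree of contrast media and does not exhibit quality issues". No criterion concerns whether Brock can be calculated or is used.

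Under Data collection, the score is produced by the study after enrolment: "Authorised research staff will then log into VNC, select the nodules of interest and record the LCP score for that nodule". For option 1 the clinical team then receives it, and "Their decision on the next management step, had they been guided by the LCP score, will then be recorded in the eCRF". The AI model section describes option 2 as "LCP-CNN alone as a threshold-based rule-out recommendation (AI binary decision to discharge or not"; options 1 and 3 leave the decision with the physician. Option 3 is evaluated at a separate research meeting after follow-up. The Statistical analysis section plans an odds ratio with a 95% CI and a two-sided p value for every outcome measure.

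**The concern.** An adherence comparison is informative only if both sides can fail. Standard care fails whenever Brock is not used, and the article itself accepts that routine practice sometimes departs from the guideline. LCP can fail in two ways: the score cannot be computed, or it is ignored. Eligibility largely closes the first way before anyone is counted. Under option 2 the second way does not exist.

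What is at stake is how a reported gain would be read. The Introduction describes a real-world evaluation meant to show whether LCP should become the standard of care, and the Abstract says the results will inform procurement. A gain that comes partly from patient selection and study procedure could be taken as evidence that the tool improves adherence in all patients with incidental nodules.

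**Working it through.** The article states no expected adherence rate, no rate of non-computable scans and no rate of ignored scores. There is no planned figure to reproduce, so the check follows the definitions and then uses labelled assumptions.

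**Step 1. Failure routes on each side**

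| Arm | Not computable | Ignored or not used |
|---|---|---|
| Standard care (Brock) | no eligibility filter | open: Brock not used in routine care |
| Option 1 | largely closed by Box 1 | open, but the score is supplied and a decision guided by it is requested |
| Option 2 | largely closed by Box 1 | closed: no physician decides |
| Option 3 | largely closed by Box 1 | open: the physician decides |

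The first route is largely closed, not fully. The criteria cover acquisition and image quality, while the score is generated after enrolment, so processing can still fail.

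**Step 2. LCP use as a formula**

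Let c be the share of otherwise eligible patients in whom LCP cannot be computed, and i the share of computable scores that are ignored.

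- Without the filter: LCP use = (1 − c)(1 − i).
- With the filter (c taken as 0): LCP use = 1 − i.
- Inflation = (1 − i) − (1 − c)(1 − i) = c(1 − i).

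Assumed values for illustration:

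| c | Option 2 (i = 0): unfiltered → filtered | Options 1 and 3 (i = 10%): unfiltered → filtered |
|---|---|---|
| 5% | 95% → 100% (5 points) | 85.5% → 90% (4.5 points) |
| 10% | 90% → 100% (10 points) | 81% → 90% (9 points) |
| 20% | 80% → 100% (20 points) | 72% → 90% (18 points) |

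For options 1 and 3 the filtered rate is still set by i: 95%, 90%, 80% or 70% for i = 5%, 10%, 20% or 30%.

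**Step 3. Brock as fallback**

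Table 1 names Brock or LCP and does not say how to count a patient whose LCP cannot be computed but in whom Brock is then used. If that patient counts as a success and Brock use is b, the inflation for option 2 falls to c(1 − b). With c = 10% and an assumed b = 60%, that is 0.10 × 0.40 = 4 points instead of 10.

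**Step 4. What the planned statistics show for option 2**

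Each patient contributes a pair. Let n10 be the pairs with LCP used and Brock not used, and n01 the reverse. If LCP use is 100%, n01 = 0. The paired odds ratio n10/n01 then has no finite value, and n10 is simply the number of patients in whom Brock was omitted. As an illustration, an exact McNemar test (my choice; the article names no test for this outcome) gives p = 2 × 0.5^n10 when n01 = 0. At n10 = 6 this is 2/64 = 0.031. Six omissions among 2000 patients (0.3%) would be significant, whatever the tool does.

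**The case against.** The strongest reply is that testing a device on scans meeting its input requirements is an ordinary choice of population that limits generalisability and nothing more. The outcome is secondary, its wording speaks only of a potential effect on possible adherence, and the strengths and limitations list already calls some secondary analyses exploratory. This bears on severity. But that exploratory label is given for sample-size reasons, and nothing in the article limits the adherence conclusion to LCP-compatible scans.

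A reader might infer that all three options score near 100% by design, so that the comparison is always 100% minus Brock use. The article does not support this. In options 1 and 3 a physician can set the score aside, and Table 1 counts that as failure. For option 1 the request for a decision guided by the score pushes the rate upward, but that is prompting, not eligibility, and it does not fix the value.

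A reader might also infer that the adherence gain is overstated by as many points as the assumed share of unusable scans. That restates the assumption. It further needs Brock use to be the same in excluded patients and no fallback to Brock, and the article settles neither.

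Two tempting repairs also meet fair objections. Adding screened-out patients to the LCP denominator alone would break the within-patient comparison, because their Brock use would be unknown. Redefining adherence as agreement with the BTS-recommended step makes a different, debatable outcome: Brock is the model used in the UK for these nodules, so departures from it could count as non-adherence even where LCP is better. The article already foresees that comparison under Data collection: "In this way, AI-guided management can be compared with BTS-compliant management".

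**Conclusion.** The point holds in a limited form. The not-computable category is largely emptied by eligibility on the LCP side only. For option 2 LCP use is about 100% by construction, so its odds ratio and p value measure only how often Brock was omitted. For options 1 and 3 the rate is 1 − i, unfixed by eligibility, with upward pressure in option 1 from the way the decision is elicited.

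The size of the inflation cannot be derived from the article. It is c(1 − i) in LCP use if non-computable patients count as failures, and smaller if Brock serves as fallback. It carries over to the difference from standard care only if Brock use is similar in the excluded patients. The plan should be changed on this point, but the primary discharge comparison does not depend on this outcome.

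**What to change.** 1. Remove option 2 from the comparative test for this outcome, or report it descriptively and state that it is 100% by construction among computable scans.
2. Record on the screening log how many otherwise eligible patients failed the software-acquisition or CT-quality criteria. Report LCP availability with them included as a separate sensitivity figure, and keep the paired comparison in enrolled patients.
3. Limit the adherence conclusion to patients with LCP-compatible scans.

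The cost is anonymous counts on the screening log and a change to the Table 1 wording. No extra patient contact is needed. The downside for the sponsor is a less favourable LCP figure.

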### Ground truth diagnosis

Patients will be classified into whether they have benign or malignant nodules as follows:

Benign-nodule patients:By resolution or stability of all qualifying incidental pulmonary nodules as determined from volumetry-based measurement on imaging follow-up over 12 months.By histopathology from biopsy or surgery of all qualifying incidental pulmonary nodules (within 12 months of baseline CT scan).Malignant-nodule patients:By histopathology from biopsy or surgery (within 12 months of baseline CT scan) of at least one qualifying incidental pulmonary nodule.Probable benign-nodule patients:By resolution, stability or shrinkage of qualifying incidental pulmonary nodules that are not in ground-truth outcomes #1 or #2 above as determined from volumetry-based measurement on imaging follow-up conducted between 3 and 12 months after the baseline CT scan.By resolution, stability or shrinkage of qualifying incidental pulmonary nodules that are not in ground-truth outcomes 1 or 2 above as determined from diameter-based measurement on imaging follow-up conducted 12 months after the baseline CT scan (supplemented with a volume-based measurement of the nodule that will be performed for research purposes).Probable malignant-nodule patients:By clinical diagnosis of lung cancer, in whom a biopsy or resection is not possible, based on high clinical probability and who are registered at a lung cancer MDT/and/or receive non-surgical treatment (stereotactic ablative radiotherapy (SABR)/radiotherapy/microwave ablation).

Volumetry-based measurement of nodule stability—and hence a benign diagnosis—will be satisfied if the lung nodule volume on the follow-up CT scan was <125% of the lung nodule volume on the baseline CT scan.

If the standard care at a particular site does not incorporate volumetry-based measurements, the volumetric measurement will be applied as part of the research study to the relevant follow-up CT scans.

Any lung nodule patients who do not fall into either of the two ground-truth outcomes 1 or 2 above will be considered to have an indeterminate diagnosis at the time of analysis and will be analysed with and without the inclusion of the ground-truth outcomes in 3 and 4.

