## Ethics and dissemination

This study has been reviewed and given a favourable opinion by the South Central—Oxford C Research Ethics Committee in UK (REC reference number: 22/SC/0142).

Given the study’s observational nature, we do not envisage any elevation to the harms or the risk of harm for patients. The sponsor and chief investigator have conducted a full risk assessment.

Patients will be asked to give their consent to participate in the study (including the analysis of standard-care CT scans, associated data collection and the healthcare economics assessment) by telephone or face to face when attending routine clinic appointments. No additional patient visits, scans or procedures are planned for the study. Patients not wishing to participate in the health economics assessment may still participate in the study’s CT imaging analysis.

The findings of this study will be shared with the funder (NHS Accelerated Access Collaborative). Results will be presented at academic and clinical conferences. The study will result in at least one peer-reviewed publication of the findings in an international medical journal.

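### CT, PET/CT, biopsy and excision use is compared only in patients whom actual care has verified as benign, so the CT percentage and the net scans avoided are biased in favour of LCP

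*Protocol article*

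**What the plan says.** The scan and procedure rows of Table 1 (Outcome measures) are differences between standard care and the three LCP options. Each is restricted to one diagnostic class: "No and percentage of CT scans and PET/CT scans performed on benign-nodule patients", and then "No and percentage of non-surgical biopsies performed on benign-nodule patients. No and percentage of surgical excisions on benign-nodule patients".

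Ground truth diagnosis gives two ways into the benign class:
- **Imaging:** "By resolution or stability of all qualifying incidental pulmonary nodules as determined from volumetry-based measurement on imaging follow-up over 12 months".
- **Tissue:** "By histopathology from biopsy or surgery of all qualifying incidental pulmonary nodules (within 12 months of baseline CT scan").

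The probable-benign class also needs a later scan, either by volumetry "on imaging follow-up conducted between 3 and 12 months after the baseline CT scan" or by diameter at 12 months. Patients outside the definite classes "will be considered to have an indeterminate diagnosis at the time of analysis and will be analysed with and without the inclusion" of the two probable classes. Ethics and dissemination states: "No additional patient visits, scans or procedures are planned for the study".

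**The concern.** Whether a patient belongs to the analysed class depends on the care being counted. Patients with benign nodules who are discharged at baseline and never imaged or biopsied again cannot enter it. This is an expected group: discharge of benign-nodule patients straight after the baseline scan is a primary outcome, and the Sample size section assumes that the Brock threshold alone discharges 13.5% of benign nodules.

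The loss is one-sided for the comparison. Patients whom standard care follows and LCP would discharge can enter the class, so LCP's savings are seen. Patients whom standard care discharges and LCP would follow cannot enter, so LCP's added scans are not seen. The planned analysis with and without the probable classes does not help, because probable-benign status also requires a follow-up scan. Service utilisation is part of the study's title, and the stated aim is evidence on whether LCP should become standard care. A net difference that omits LCP's added follow-up could mislead on that question.

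**Working it through.** **Inputs (Sample size section).** Among benign nodules, 17.0% are discharged by LCP but not Brock, and 13.5% by Brock but not LCP. The protocol takes Brock to represent standard care.

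**The plan's own figure.** The protocol gives no figure for scan or procedure use; the nearest is the benign-group sample size of 2026 at 80% power. Two-sided 0.05 is assumed here, as 0.05 is stated only for the cancer calculation.
- Normal-approximation McNemar: n = (1.960·√0.305 + 0.8416·√(0.305 − 0.035²))² / 0.035² = 1952.
- The exact test gives 80.4% power at 2026, so the stated figure is reproduced.
- The odds ratio 17.0/13.5 = 1.26 also agrees.

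**Assumptions for the illustration.** Actual care equals the Brock rule. Patients discharged by standard care get no later scan or tissue. Everyone else completes follow-up and enters the class. The share b discharged by both rules is not given, so it is varied from 0 to 40%. Here followed means not discharged after the baseline scan; it is not a count of scans per patient.

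**Formulas.**
- All truly benign patients: standard care follows 100 − 13.5 − b; LCP follows 100 − 17.0 − b; the difference is 3.5 points for any b.
- Verified class, of size v = 100 − 13.5 − b: standard care follows 100%; LCP follows 100 × (1 − 17.0/v); the apparent difference is 100 × 17.0/v.

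| b | All benign: standard care, LCP, net | Verified class: standard care, LCP, net |
|---|---|---|
| 0% | 86.5, 83.0, 3.5 | 100, 80.3, 19.7 |
| 20% | 66.5, 63.0, 3.5 | 100, 74.4, 25.6 |
| 40% | 46.5, 43.0, 3.5 | 100, 63.4, 36.6 |

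**As counts.** Per 1000 truly benign patients, the true net number spared follow-up is 170 − 135 = 35. The class shows 170, because the 135 whom LCP would add are absent.

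**Raw standard-care numbers.** Patients without scans add zero, so leaving them out does not raise the number. At b = 0, 865 per 1000 are followed. If 10% or 20% of patients have only partial follow-up and miss the strict class, it holds 765 or 665, which is an undercount.

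**Biopsies and excisions.** Suppose a true benign-procedure rate of 3%, with a share f of the other benign patients verified by imaging and a share g of those with a procedure captured in the class. None of these is in the document. The class rate is 0.03g/(0.03g + 0.97f). With g = 1 and f = 0.8 it is 3.7%; with g = 0.6 and f = 0.8 it is 2.3%. The first lies above 3% and the second below.

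**The case against.** The strongest reply is that both options are assessed in the same patients, so a smaller denominator would scale both percentages alike and leave the number avoided unchanged. That would hold if the lost patients were concordant. They include every patient whom only standard care discharges, so the number avoided changes too: 170 against 35 per 1000 in the illustration. This also answers a literal reading of the percentage as the share of all scans that fall on benign patients, since the count does not depend on the denominator. Incomplete follow-up would remove some of LCP's savings as well, but it would have to remove 135 of the 170 (79%) before the count came back to 35.

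A reader might infer more than the documents support:
- **That all standard-care use is overstated.** The outcome is number and percentage, and the number is not inflated.
- **That biopsy and excision rates are inflated.** Histology must cover all qualifying nodules, so a patient with one of several nodules sampled, or a non-diagnostic biopsy, does not enter by that route. Adding the probable-benign class and applying research volumetry also recovers unbiopsied patients. Size and direction are therefore open. PET/CT is not named as an entry route.
- **That the cost comparison inherits the bias.** Table 1 defines cost over all activity for lung nodules or suspected lung cancer, without a benign restriction, and nothing says that the benign rows feed it.

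It is also fair that restricting to benign patients targets unnecessary procedures, and that extra denominators often belong in an analysis plan. But this protocol itself fixes both the outcome population and the class definition, so the problem lies in what is stated.

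**Conclusion.** The concern holds for two quantities: the percentage of benign-class patients with CT follow-up, and the net difference in scans between standard care and LCP. Both are biased in favour of LCP because benign patients discharged by standard care without later imaging or tissue cannot enter the class, and the planned with/without analysis cannot reveal this.

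On the protocol's discordance rates, a true net reduction of 3.5 points would appear as 19.7 to 36.6 points. This is an illustration. It rests on actual care matching the Brock rule, on no later scan after discharge, and on a both-discharged share of 0 to 40% that the document does not give. Data collection lets the team modify management after seeing the score; any discharged patient who is then imaged could enter the class, which would shrink the gap.

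The conclusion does not extend to the raw number of standard-care scans, to a stated direction for biopsies and excisions, or to the cost outcome.

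**What to change.** In Table 1:
- Report the differences in CT, PET/CT, non-surgical biopsies and excisions over all enrolled patients, including those discharged by standard care whom LCP would follow.
- Report procedures with benign histology over all enrolled patients as the avoidable-procedure measure.
- Keep the benign-class rows alongside, with a note that entry to the class requires a follow-up scan or histology.

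The cost is small. The eCRF already takes "Other data points necessary to evaluate service utilisation (eg, additional scans, biopsies and treatments for lung nodules or lung cancers"), together with the standard-care and score-guided decisions; the threshold options are evaluated in a batch at the end. LCP's added scans must be derived from the hypothetical decisions, as must the rest of the LCP side in a study that does not set out to change care. One downside is that the all-enrolled count includes appropriate work-up in patients with cancer. The benign-histology measure and the retained benign-class rows keep the view of unnecessary procedures.
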